## Method/design

### Recruitment

Participants will be a large, randomly selected representative sample of the adult Scottish general public. These participants will be randomly selected from a list containing 1.2 million members of the adult Scottish general public. Participants will be posted a brief questionnaire, together with information about, and a link to the UK Organ Donor Register. We will be receiving informed consent from all participants. However, we were concerned that if we were to require all participants to return signed consent forms by post, it is likely that people who are more likely to register as an organ donor would be more likely to participate in our study. This would create an unacceptable bias that could render our results scientifically meaningless. We are, therefore, using an 'opt-out' approach in which participants are required to contact us if they do not want to take part in the study. We will make it very clear that people do not have to participate if they do not wish to, and we have made it as easy as possible to withdraw either by; (a) ticking a form and returning it to us in the stamped addressed envelope that we provide to all, (b) email or (c) telephone. We believe that our approach is justified as; (a) no harm will come to the participants, (b) our research cannot be practically carried out if we had to receive written informed consent from all participants, (c) the potential benefits to the NHS (i.e. determining effective methods of increasing organ donor registrations) outweigh the cost, and (d) NHSBT will be conducting the search of the organ donor register, not us, we will never have access to individual identifiable results, and we will never know whether a specific individual has registered or not, only NHSBT will have this information, and crucially, they would have it regardless of whether this study was conducted or not.

Based on our pilot data [11], we estimate that in order to identify a significant effect at the conventional .05 alpha level, at a power of .80, we would need 565 completed questionnaires per condition. As with any questionnaire based study there are likely to be many people who do not complete our survey. The response rate for this type of survey ranges from 23% to 37% [37]. Based on the conservative lower estimate (23%), we calculate that we would need to distribute 2,460 questionnaires per condition in order to gain a sufficient number of completed surveys. Furthermore, we also need to oversample to account for the proportion of the adult Scottish general public that are already registered donors. Adjusting for this, we need to distribute 3,630 surveys per condition in order to gain a sufficient number of completed surveys. Because there are four conditions in this study (for details, see below), we need to distribute a total of 14,520 questionnaires. The logistics of this national field based study will be conducted by Perspektiv, a market research company (http://perspektivred.co.uk). It should be noted that in the present study we improve on O'Carroll et al. [11] by including a no questionnaire control arm. We do not have pilot data that would allow us to conduct power calculations for this condition. However, based on the questionnaire control arm in O'Carroll and colleagues [11], we estimate that the above sample size estimates should be more than sufficient.

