### Pilot studies

The aim of the present study is to determine whether simply asking people whether they would later regret not registering as an organ donor increases verified registration. In preparation, we have conducted 3 pilot studies [for full details, see 11,12]. We found that simply asking people whether they would later regret not registering as an organ donor increased their intentions to register [12, Study 2]. Moreover, we replicated this finding with a more representative sample of the adult Scottish general public [12, Study 3]. Although these findings are promising, people do not always act upon their intentions, the well recognised intention-behaviour gap. In a third pilot study we found that asking people whether they would later regret not registering as an organ donor increased self-reported organ donor registration [11]. This latter finding suggests that anticipated regret promotes organ donor registration. However, this research can be criticised for using self-reported measures of registration. The acid test is clearly whether this intervention leads to a significant increase in *verified *registrations on the UK NHS Blood and Transplant (NHSBT) posthumous Organ Donor Register. The aim of the present study is to test whether a large scale, simple anticipated regret intervention leads to a significant increase in NHSBT verified organ donor registrations.

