### Analyses

Our primary analysis will be a logistic regression predicting donor status (registered vs. not registered) to explore the proportion of respondents who have registered as organ donors 6 months later as a function of the 4 arms. In this analysis we will control for any potential between-arm differences in age, gender and socio-economic status, if these are related to the outcome. We will conduct this regression with all participants who have not opted out of the study, regardless of whether or not they returned the questionnaire. Participants may not comply with their random assignment. That is, in this case, for some reason not complete and return the questionnaire. We will use instrumental variables (IV) regression techniques to estimate the causal effect of the intervention in compliers [see [38,39]]. Here randomization acts as the instrumental variable, compliance status as the endogenous variable. This technique is a viable alternative to traditional intention to treat (ITT) analysis. ITT treats randomization as a treatment, when in actuality it is the intervention, not the randomization that is the source of any effect. By treating assignment as an instrumental variable and intervention compliance as an endogenous variable, IV regression techniques reduce the bias in standard ITT analyses, and provide as estimate of the causal effect of the intervention in compliers [38]. These analyses will be conducted in M*Plus*-6 [40] and Stata [41]. We will also record the time interval between the questionnaire being sent out and date of organ donor registration to test for temporal effects.

If our intervention is successful, we will test the processes through which it occurs. We will assess whether the anticipated regret intervention promotes organ donor registration by increasing people's intentions to register and decreasing their emotions and non-cognitive affective attitudes towards organ donation. Essentially, we will test whether intentions and emotions mediate the effect of our intervention on registration. Simple tests of mediation will be implemented in ZUMASTAT [42]. More detailed tests of multiple and joint mediation as well as moderated mediation will be conducted using M*Plus*.

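### The stated 80% power belongs to a comparison of questionnaire completers, not to the primary analysis, which also includes non-returners

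*Protocol article*

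**What the plan says.** The sample size is in the protocol article under Recruitment. It takes an effect from the third pilot study and states that, at alpha .05 and 80% power, "we would need 565 completed questionnaires per condition". The mailing is sized to deliver those completers: 2,460 packs per arm at a 23% response (the low end of a 23-37% range), raised to 3,630 per arm to allow for existing donors, 14,520 in all. For the no-questionnaire control (NQC) arm the article admits that it has no pilot data for a power calculation, yet adds that "we estimate that the above sample size estimates should be more than sufficient".

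The Analyses section describes the primary logistic regression as one "to explore the proportion of respondents who have registered as organ donors 6 months later", and two sentences later says that it will be run "with all participants who have not opted out of the study, regardless of whether or not they returned the questionnaire". Exclusion criteria removes existing donors and active withdrawals from the main analyses. Analyses adds IV regression, with randomisation as the instrument and failure to complete and return the questionnaire as non-compliance. Evaluation says that effectiveness will be judged by the IV analyses.

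No expected registration rate, effect size or power is given for the all-participants regression or for the IV analysis.

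**The concern.** The power calculation treats non-returners as postage loss, whereas the primary analysis keeps them in the denominator. If the questions work only in people who answer and return them, the between-arm difference in the primary set is the completer difference multiplied by the response rate. The larger number of people analysed need not make up for that.

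Research question (a) asks whether there is a significant increase, so a reader of a null result would rely on the 80%. Research question (c) uses the observed effect to plan a UK-wide study, so a confusion between an effect in returners and an effect in all participants would carry forward.

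**Working it through.** **1. The plan's own figures.** 565 / 0.23 = 2,457, stated as 2,460. 4 x 3,630 = 14,520. The step from 2,460 to 3,630 implies 1 - 2,460/3,630 = 32.2% already registered. The Background gives 38% for Scotland, which leaves 3,630 x 0.62 = about 2,250 non-donors per arm. I use both 2,250 and 2,460, before opt-outs, whose number is not given. The 565 itself cannot be reproduced, because no rates are stated.

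**2. Effects consistent with 565.** Two-proportion normal approximation, two-sided .05 (the article does not state the sidedness), 80% power. I assumed a control rate among completers and solved for the other rate: 2% vs 5.1%, 5% vs 9.3%, 10% vs 15.6%, 20% vs 27.1%, 40% vs 48.3%. These are assumptions, not the plan's figures.

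**3. Equal-variance shortcut, effect in returners only.** With response rate r and n non-donors per arm, the expected test statistic is 2.80 x r x sqrt(n/565).
- r = 0.23, n = 2,460: 2.80 x 0.23 x 2.087 = 1.34, so power is Phi(1.34 - 1.96) = 27% (33% if one-sided).
- r = 0.23, n = 2,250: 1.29, power 25%.
- r = 0.37, n = 2,460: 2.16, power 58%.
- Non-donors per arm needed for 80%: 565/0.23² = about 10,680, or 565/0.37² = about 4,127.

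**4. Binary outcome.** The rate in each arm is r x p + (1 - r) x q, where p is the completer rate and q the non-returner rate. Example with p = 5% vs 9.29%, q = 2.5%, r = 0.23, n = 2,460: the arms have 3.08% vs 4.06%, a difference of 0.99 points. The standard error is 0.53 points, so power is Phi(0.99/0.53 - 1.96) = 46% from unrounded values.

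Power over completer control rates of 2-40%, with no effect in non-returners:

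| Non-returner rate relative to completer control rate | 23%, n = 2,250 | 23%, n = 2,460 | 37%, n = 2,250 | 37%, n = 2,460 |
|---|---|---|---|---|
| zero | 56-75% | 60-79% | 79-92% | 83-94% |
| half | 31-48% | 33-51% | 62-79% | 66-83% |
| same | 25-35% | 27-37% | 55-68% | 59-71% |

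**5. Some effect in non-returners.** Under equal variance with n = 2,460, 80% needs an average effect of sqrt(565/2,460) = 0.479 of the completer effect. At 23% response, non-returners must show (0.479 - 0.23)/0.77 = 32% of it; at 37%, (0.479 - 0.37)/0.63 = 17%. In the binary calculation at 23% response, with non-returners registering at the completers' control rate, a quarter of the effect gives 66-81% and half gives at least 93%. Where non-returners seldom register, a smaller share is enough.

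**6. The IV analysis.** With randomisation as the instrument, the estimate is essentially the all-participants difference divided by the difference in compliance, and its standard error is scaled by nearly the same factor. The test statistic, and so the power, is about that of the all-participants comparison.

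**The case against.** A reader might infer that power falls to between a quarter and three quarters as a matter of fact, and that the trial would probably miss its planned effect. The documents do not support that. The range needs a completer control rate, a non-returner rate, no effect in non-returners, and 23% response. Only the last is stated, and the article presents it as the cautious end of 23-37%. Non-returners are sent the same items, and some may read or answer them without posting them back. In several scenarios power exceeds 80%, and in others detection is still more likely than not. Nor can one say how many percentage points were planned, because the article gives none.

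It would also be too broad to say that everyone mailed is analysed: existing donors and opt-outs are excluded. In addition, the all-participants wording comes two sentences after *respondents*, so the intended set is clear enough, and the article is candid about the missing NQC pilot data.

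All of this stands, and it limits the size that can be claimed. It does not restore the 80%. No effect of assignment in non-compliers is what the article's own IV model needs, so that scenario cannot be set aside. At 23% response, power under it is below 80% in every case examined.

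That the pilot outcome was self-reported, of which the article says "this research can be criticised for using self-reported measures of registration", is a separate and smaller limitation. The conclusion here does not depend on it.

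**Conclusion.** The point holds as a mismatch between two stated elements: the only power figure is for 565 completers per arm, and the primary regression and the deciding IV analysis use a different set. The 80% is not shown for either.

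The size is conditional. It rests on effects that give 80% at 565 per arm, assumed control rates of 2-40%, no effect in non-returners, and about 2,250 to 2,460 non-donors per arm before opt-outs. Power is then about 25-79% at 23% response and about 55-94% at 37%. At 23% it reaches 80% only if non-returners also respond, at roughly a third or more of the effect under equal variance. I am confident of the mismatch; the documents cannot fix a single power figure. Choosing the all-participants set as primary is sound and is not criticised.

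**What to change.** - Keep the all-participants analysis as primary.
- In Recruitment, state that 565 per arm applies only to a comparison of returners.
- Replace the power statement with power, or a detectable difference, for the primary set and for the IV analysis. Base it on the investigators' own expected registration rates in returners and non-returners, over 23-37% response, and state what effect is assumed in non-returners.
- In Analyses, change *respondents* to: all randomised participants not registered at mailing who have not opted out.
- For the NQC arm, replace the assurance of sufficiency with its power on the same basis.

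The cost is a recalculation, a few wording changes and probably a less favourable stated power. No extra mailing is needed.

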#### Exclusion criteria

We are primarily interested in whether a simple anticipated regret intervention increases organ donor registration. We will, therefore, exclude people who are already registered organ donors from the main analyses. We will also exclude participants who actively withdraw from the study.

### Design and materials

We will utilise a between-groups, prospective randomised controlled design (i.e. participants will be randomly allocated into one arm of the study). In line with previous research [11,12,18,34], we will manipulate anticipated regret by altering the questions that the participants complete. Participants will be randomly allocated into one of four conditions: no questionnaire control (NQC), questionnaire control (QC), theory of planned behaviour (TPB) questionnaire, and anticipated regret (AR) questionnaire (for an overview, see Figure 1). The latter three conditions are similar to O'Carroll and colleagues [11].

**Figure 1 F1:**
[figure not shown]
**CONSORT flowchart of trial design**.

#### No questionnaire control (NQC)

This extension of O'Carroll and colleagues [11] has been added to determine whether simply being contacted increases organ donor registration. This arm will simply receive a letter, donor registration form and questions collecting demographic information (e.g., date-of-birth, gender, occupation and postcode for socio-economic status estimation).

#### Questionnaire control (QC)

This arm will receive the same materials as the NQC arm plus a questionnaire measuring their emotions and non-cognitive affective attitudes towards organ donation [10-12]. This questionnaire will measure 5 emotions and affective attitudes: the ick and jinx factors, bodily integrity, medical mistrust, and perceived benefit. The ick factor will be measured using three items (e.g. "The thought of organ donation makes me uncomfortable"). Three items will be used to measure jinx (e.g. "The surest way to bring about my own death is to make plans for it like signing an organ donor card"). Two items will measure bodily integrity (e.g. "The body should be kept whole for burial"). There will be four medical mistrust items (e.g. "If I sign an organ donor card, doctors might not try so hard to save my life"). Perceived benefit will be measured with four items (e.g. "Organ donation helps to bring meaning to the death of a loved one"). All items will be rated on a 7-point Likert scale (1 = strongly disagree, 7 = strongly agree).

Non-donors will also be asked to complete two questions measuring their intentions to register as an organ donor in the future (e.g. "I will definitely register as an organ donor in the next few months"; 1 = strongly disagree, 7 = strongly agree). We will also include filler questions to ensure that the number of items in this arm is identical to the TPB and AR arms.

#### Theory of planned behavior (TPB) questionnaire

The TPB arm will complete the same materials as the QC arm, plus additional items measuring attitudes, perceived control, and subjective norms. Attitudes will be measured with two items (e.g. "I support the idea of organ donation for transplantation purposes"). Two subjective norm items will be included (e.g. "Most people who are important to me think I should register as an organ donor in the next few months"). The attitudes and subjective norm items will be rated on 7-point Likert scales (1 = strongly disagree, 7 = strongly agree). Three items will measure perceived control (e.g. "How much control do you have over registering as an organ donor in the next few months?"; 1 = no control, 7 = complete control). Once again, non-donors will also be asked to rate their intentions to register as a donor, using the items described above. We will also include filler questions to ensure that the number of items in this arm is identical to that of the QC and AR arms.

#### Anticipated regret (AR) questionnaire

This arm will complete the same indices as the TPB arm, plus two items measuring anticipated regret: "If I did not register as an organ donor in the next few months I would feel regret" (1 = definitely no, 7 = definitely yes) and "If I did not register as an organ donor in the next few months, I would later wish I had" (1 = strongly disagree, 7 = strongly agree). Non-donors will also be asked to complete the intention indices described above.

#### Organ donor registration

Participants in all four arms of the study will be told how to register as an organ donor online, and by telephone, post and text message. All participants will also receive a NHSBT organ donor registration form.

### Outcomes

Our primary outcome variable is verified organ donor registration within 6 months of our postal intervention. Crucially, NHSBT has agreed to collaborate with us and perform a secure and confidential search of their organ donor register 6 months following our brief postal intervention. This search will tell us whether or not the participant is a registered organ donor and, if applicable, when they registered. NHSBT will conduct this anonymised search for all participants who have not opted out of the study, regardless of whether or not they returned the questionnaire. This will allow us to determine whether there is any bias caused by people being more willing to complete the questionnaire in certain conditions.

Our second outcome is intentions to become an organ donor in the future. If our anticipated regret intervention is successful we will test whether the increase in registration is due to participants having greater intentions to register as an organ donor. This outcome will be measured in our questionnaires, using the indices described above.

### Analyses

Our primary analysis will be a logistic regression predicting donor status (registered vs. not registered) to explore the proportion of respondents who have registered as organ donors 6 months later as a function of the 4 arms. In this analysis we will control for any potential between-arm differences in age, gender and socio-economic status, if these are related to the outcome. We will conduct this regression with all participants who have not opted out of the study, regardless of whether or not they returned the questionnaire. Participants may not comply with their random assignment. That is, in this case, for some reason not complete and return the questionnaire. We will use instrumental variables (IV) regression techniques to estimate the causal effect of the intervention in compliers [see [38,39]]. Here randomization acts as the instrumental variable, compliance status as the endogenous variable. This technique is a viable alternative to traditional intention to treat (ITT) analysis. ITT treats randomization as a treatment, when in actuality it is the intervention, not the randomization that is the source of any effect. By treating assignment as an instrumental variable and intervention compliance as an endogenous variable, IV regression techniques reduce the bias in standard ITT analyses, and provide as estimate of the causal effect of the intervention in compliers [38]. These analyses will be conducted in M*Plus*-6 [40] and Stata [41]. We will also record the time interval between the questionnaire being sent out and date of organ donor registration to test for temporal effects.

If our intervention is successful, we will test the processes through which it occurs. We will assess whether the anticipated regret intervention promotes organ donor registration by increasing people's intentions to register and decreasing their emotions and non-cognitive affective attitudes towards organ donation. Essentially, we will test whether intentions and emotions mediate the effect of our intervention on registration. Simple tests of mediation will be implemented in ZUMASTAT [42]. More detailed tests of multiple and joint mediation as well as moderated mediation will be conducted using M*Plus*.

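### The primary regression is declared for everyone who has not opted out, but its covariates have no stated source except the mailed form, and whether they enter depends on the outcome data

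*Protocol article*

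**What the plan says.** The Analyses section specifies a logistic regression of donor status at 6 months on the four arms. On adjustment it says: "we will control for any potential between-arm differences in age, gender and socio-economic status, if these are related to the outcome". On the analysis set it says: "We will conduct this regression with all participants who have not opted out of the study, regardless of whether or not they returned the questionnaire".

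The demographic variables appear in one other place. The pack for the no questionnaire control arm contains "questions collecting demographic information (e.g., date-of-birth, gender, occupation and postcode for socio-economic status estimation". The other arms build on that pack. For the questionnaire control arm: "This arm will receive the same materials as the NQC arm plus a questionnaire". The planned behaviour arm adds items to that, and the anticipated regret arm adds items to the planned behaviour arm.

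Under Outcomes, the register search covers everyone who has not opted out, so the outcome is known for non-returners. That section gives as a reason that willingness to complete the questionnaire may differ by condition. Exclusion criteria removes people already registered from the main analyses. Recruitment describes a list of 1.2 million adults but not the fields it holds.

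**The concern.** There are two problems.

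**Covariate source and analysis set.** The outcome is obtained for all. Date of birth, gender, occupation and postcode are, as far as the article shows, obtained only from people who send the form back. A regression that needs these values and is fitted to complete cases contains returners only. Returning the form happens after randomisation and may depend on arm: the four packs differ, and the no questionnaire pack is the shortest. The register search was extended to non-returners in order to expose this bias, and adjustment by form-only covariates would bring it back into the primary estimate.

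**The trigger.** Covariates enter if arms differ on them and if they are related to the outcome. On a looser reading only the second condition binds. Either way, if the relation is judged in the trial's own data, it is unknown until the register has been searched. The primary model is then chosen after the outcomes are seen. In a logistic model the choice also affects what is estimated, since an odds ratio conditional on covariates is not the same quantity as the unadjusted one.

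**Working it through.** **Inputs from the protocol article**
- Recruitment: 565 completed questionnaires per condition; response rate 23% to 37%, with 23% used for planning; 2,460 and then 3,630 mailed per condition; 14,520 mailed in total.
- Background: 38% of people in Scotland already registered.

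**Reproducing the plan's figures**
- The article states: "Based on the conservative lower estimate (23%), we calculate that we would need to distribute 2,460 questionnaires per condition". Check: 565 / 0.23 = 2,457, which agrees with 2,460 after rounding.
- 4 × 3,630 = 14,520, as stated.
- The step to 3,630 does not reproduce with 38%: 2,460 / (1 − 0.38) = 3,968. The figure 3,630 implies 1 − 2,460 / 3,630 = 32.2% already registered. This is a separate matter, used below only as a sensitivity check.

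**What a complete-case adjusted model would keep**

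Formula: kept = mailed × (1 − proportion already registered) × return rate.

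| Set | Eligible | Kept at 23% | Kept at 37% |
|---|---|---|---|
| All mailed, four arms | 14,520 | 3,340 | 5,372 |
| Unregistered per arm, 38% registered | 3,630 × 0.62 = 2,251 | 518 | 833 |
| Unregistered per arm, 32.2% registered | 3,630 × 0.678 = 2,461 | 566 | 911 |

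The share lost is 63% to 77% in every row. The table assumes the same return rate in all arms and among registered and unregistered people, and it ignores opt-outs, for which the article gives no figure.

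The retained number is close to the 565 per condition for which the study was sized, so the main loss is not the count. What is lost is the all-randomised comparison that the declared analysis set was meant to secure.

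**Timing of the trigger**

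Research ethics and timetable puts completion of the analytic strategy in months 7 to 12 and the register check in months 13 and 14. A rule that needs the relation between covariates and the trial outcome cannot be resolved to a covariate list until after that check.

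**The case against.** The strongest reply is that the article never specifies complete-case analysis and states the opposite intent, since the regression is to run "with all participants who have not opted out of the study, regardless of whether or not they returned the questionnaire". A reader might infer that adjustment drops 77% of those mailed and makes the primary analysis returner-only. The documents do not support that as a fact, for four reasons:
- The form is the only stated source, but the article does not say it is the sole one. Packs are posted, so an address is held for everyone, and an area-based socio-economic measure is presumably obtainable. Whether the list or the register linkage supplies age and gender is not stated.
- Imputation or similar methods would reconcile the two sentences, so they are not strictly incompatible. Such methods are commonly left to the analysis plan, and their absence from an article is not an error.
- Adjustment is conditional, so the final model might contain no covariates and lose nobody.
- 77% is the worst end of the stated range.

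All four stand and make the first problem conditional. A reader might also carry the problem into the instrumental variables analysis, but the article does not say which covariates enter there.

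On the trigger, it can be said that with about 2,250 unregistered people per arm, chance imbalance in three demographic variables should be small and the effect on an all-participant estimate probably minor. It can also be said that a relation to the outcome might mean one known beforehand. The first point limits the likely harm. The second would allow the covariates to be listed now, and the sentence does not say it. Neither makes this a good way to fix a primary model.

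**Conclusion.** The point holds in conditional form. The adjustment and the declared analysis set do not fit together for the 63% to 77% expected not to reply, unless covariates for them come from a source the article does not name or are imputed. If neither happens and complete cases are used, the adjusted model would keep about 518 to 833 of about 2,250 unregistered people per arm, selected after randomisation. This rests on the article's response range and its 38% registration figure.

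The size of any resulting bias cannot be given, because the documents contain nothing on how reply relates to willingness to register in each arm.

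The trigger is a weakness even if every covariate is available for everyone. It is a stated rule rather than an omitted detail, and it leaves the primary covariate set open until outcomes are known. Its effect on error rates has not been quantified and is probably small if the all-participant set is kept.

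**What to change.** Choose one of these before the register search:
1. Make the unadjusted comparison of arms primary, in all previously unregistered participants who have not opted out.
2. Always adjust for a named set held for everyone mailed, for example area deprivation from the mailing postcode, plus age and gender if the list holds them, whatever the observed imbalance or association.

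In either case, delete the trigger on between-arm differences and relation to the outcome, and use the demographics collected on the form only in returner analyses, labelled as such.

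The cost is a change of wording and, for the second option, attaching a deprivation score to addresses already held. The downside is slightly less covariate detail, since individual occupation would not be in the primary model.
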